##### Patient diaries

Patient out of pocket and health system costs associated with each arm of the trial will be estimated using an online monthly resource use diary [51, 52]. The diary will be used to document and measure health service use - such as melanoma clinic visits, other health practitioner consultations, imaging and other tests, hospital visits, and time taken to take and submit images for teledermatology. We will ask patients to report the number of trips made to their melanoma follow-up clinic and the mode of transport used. We will also ask patients to report any visits to other physicians for a skin lesion excision or other skin cancer-related procedures. The time each patient spends to take and submit images, and check teledermatology reports (intervention group) will be recorded. The diary will also document informal caregiver (carer) days out-of-role (including paid and unpaid work), travel costs and direct carer costs.

##### Images and teledermatology reports

At baseline and 3 monthly intervals to 12 months post randomisation, intervention participants will be asked to take images using the mobile dermatoscope attached to their phone. They will use the corresponding app for the dermatoscope on their phone to submit the images to the corresponding web-based platform where the teledermatologist, site coordinator and research study staff can view them. Teledermatologists will use the same web platform to make and submit their reports on the lesions, which are then relayed to participants through the smartphone app. The teledermatology reports are also stored on the web platform for access by the research study staff.

##### Pathology

The research study staff will review participants’ medical records to collect and upload data including documents confirming eligibility (pathology reports and/or doctors’ letters) into REDCap. They will also confirm the number of skin lesions biopsied or removed and the number of melanomas and keratinocyte skin cancers diagnosed. The research study staff will upload source information including letters and pathology reports associated with excisions. After completion of the trial, any melanomas diagnosed during the trial will be reviewed by an expert dermatopathologist who is blinded to study arm, to confirm or refute the diagnosis. These reviews will be stored on REDCap.

##### Linkage

At completion, trial data will be linked with site databases for a schedule of clinic appointments, procedures, and pathology, and with the New South Wales (NSW) Cancer Registry and the Medicare Benefits Schedule claims database.

### Plans to promote participant retention and complete follow-up {18b}

#### Participant retention and withdrawals

We will promote participant retention through regular contact with the research study staff, with SMS text, email, or phone reminders to complete study activities. We will tabulate the number of patients whose consent for trial participation is withdrawn by the participant and those who are withdrawn by the research study staff due to loss to follow-up or if they move outside of NSW. Participants may choose to withdraw from active follow-up but consent to the ongoing passive collection of data (clinic, Cancer Registry and Medicare Benefits Scheme claims database) during the follow-up period. We will present descriptive summaries for the number of people who withdraw or are lost to follow-up, with present separate results for each category (type of withdrawal and loss to follow-up).

##### End of study

Active participation will continue for 12 months following randomisation or until all trial tasks have been completed (end dates will be staggered for individual participants and they will not be able to submit data after they have finished the 12 months follow up). We will collect linked data from the clinics, Cancer Registry and Medical Benefits Scheme for a further 12 months post-trial (i.e. 24 months post-randomisation).

### Data management {19}

Data management procedures are detailed in the data management plan included as Supplementary file 2.

### Confidentiality {27}

Research data will be stored in accordance with the University of Sydney’s Research Data Management Policy and Research Code of Conduct and will be stored on University managed and/or sanctioned storage infrastructure. Data will be secured via a personal login and data elements restricted by role at the direction of the Chief Investigator. After data collection, all identifiers such as participant names will be removed and replaced by a code. Electronic data will be re-identifiable for the duration of the project. Participant contact information (phone number and email address) will be stored in a quarantined area on REDCap, only visible to members of the research team who require it for study-related contact. This restriction will be built into REDCap user roles. Personal identifiers will be removed at trial completion, and only non-identifiable data will be stored subsequently.

### Statistical methods

#### Statistical methods for primary and secondary outcomes {20a}

A detailed Statistical Analysis Plan will be published separately with a full description of the statistical methods that will be used for analysing the primary and secondary outcomes, planned additional assessments including subgroup and sensitivity analyses, and methods to manage missing data (manuscript in preparation). All analyses will adhere to the intention-to-treat principle, unless otherwise stated. As a secondary analysis, we will also estimate the effect that would have been observed had all participants adhered to the protocol.

##### Primary outcome

We will use generalised linear models to investigate the difference between patient-led and clinician-led surveillance on the proportion of participants with a subsequent new primary or recurrent melanoma diagnosed through an unscheduled visit. We will present the proportion of participants with the primary outcome in each randomised group, and the between-group difference in proportions, along with the *p* value and 95% confidence interval (CI). Unadjusted and adjusted analyses will also be presented. For the latter, we will include baseline measurements of important risk factors for new or recurrent melanoma as covariates in the model. These will include age, sex, specialist/GP clinic, melanoma substage, subsequent new primary melanoma risk score [48] and dysplastic nevus syndrome. We will check the appropriate assumptions for the model. The adjusted and unadjusted analysis will be presented as an odds ratio along with the 95% CI and *p* value.

##### Secondary outcomes

We will assess the effect of patient-led and clinician-led surveillance on the secondary outcome of time to diagnosis of a skin cancer (melanoma or keratinocyte cancer), using Cox proportional hazards models. We will present unadjusted and adjusted analyses. For the latter, we will include the same covariates as for the primary outcome (important prognostic variables for outcome event). We will check the proportional hazards assumption using visual inspection of plots (including Schoenfeld residuals) and corresponding test statistics. Other assumptions to be checked include if there is non-informative censoring and if there is a secular trend. All participants will continue to be followed up unless they have withdrawn their consent or moved interstate. In the case that they have withdrawn their consent or moved interstate, participants will be censored at the last available follow-up. The unadjusted and adjusted hazard ratios with 95% CI and *p* values will be reported. If the assumptions including the proportional hazards assumptions are violated, these will be addressed as required. The time to diagnosis will also be analysed allowing for competing risk of death.

The appropriate generalised linear model will be used to assess the remaining secondary outcomes. In general, Poisson regression will be used for count variables, logistic regression for proportions and multiple linear regression for continuous outcome variables. We will assess effects on continuous outcomes (adherence with SSE; thoroughness, confidence, beliefs, attitude and knowledge of SSE; level of fear of new or recurrent melanoma; general anxiety, stress and depression; and acceptability of reducing the frequency of routinely scheduled clinic visits) by including baseline measurement of the outcome as well as other relevant prognostic variables as covariates in the multiple linear regression model. For example, for the outcome: level of fear of new or recurrent melanoma severity, we will include baseline measurement of FCRI severity subscale and personal history of depression or anxiety as covariates. We will estimate the between-group difference in change from baseline for each outcome, together with 95% CI and *p* values. We will check the appropriate model assumptions and if any are violated, then we will use other generalised linear models.

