##### Intervention description {11a}

Trial participants in the control arm will receive clinician-led surveillance (usual care), which involves:
An educational booklet ‘Your guide to early melanoma’;Routinely scheduled clinic visits as recommended by their treating clinician (likely to be at intervals between 6 and 12 months);Unscheduled clinic visits, if needed (not prompted through teledermatology)

Trial participants in the intervention arm will receive the intervention (patient-led surveillance) as an adjunct to their usual care, including:
An educational booklet ‘Your guide to early melanoma’;Routinely scheduled visits as recommended by their treating clinician;Unscheduled clinic visits, if needed (not prompted through teledermatology);Continued access to the ASICA skin checker instructional videos on how to perform SSE (including checking for locoregional recurrence) [30, 39];A mobile dermatoscope (with a polarised or non-polarised light source) to attach to their phone, with detailed written and video instructions on how to use the smartphone app and dermatoscopeTraining for themselves and a partner/friend/support person in using the dermatoscope and app, delivered one-on-one by web conferencing;Email or SMS text reminders every 3 months to perform SSE;Teledermatology (see Fig. 2)

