#### Secondary outcomes

(M2) Time to diagnosis of a new skin cancer: time from randomisation to the histopathology diagnosis of a melanoma or keratinocyte skin cancer (as defined by the date on the histopathology report).

(M3) Pathological characteristics of new skin cancers: including thickness, stage, and other prognostic factors (melanomas and keratinocyte skin cancers).

(M4) Skin Self Examination (SSE) including:

M4.1. Thoroughness, confidence, beliefs, attitude, and knowledge of SSE will be assessed by items adapted from Janda et al. [42].

M4.2. Adherence with recommended SSE practice (total body self-examination conducted three-monthly); Participants will be asked how often they perform a complete examination of their skin.

(M5) Fear of new or recurrent melanoma (FCR) severity: assessed using a modified (i.e. melanoma-specific) version of the 9 item FCR Inventory severity subscale, the most comprehensive multi-dimensional scale of FCR available [10]. A higher score indicates greater FCR.

(M6) General anxiety, stress and depression: measured using the short version of the Depression Anxiety and Stress Scales (DASS-21) [43]. The DASS-21 is a set of three 7-item self-report scales designed to measure the emotional states of depression, anxiety, and stress.

(M7) Acceptability of hypothetical reduction in scheduled clinic visit frequency: measured through questionnaire items designed specifically for this study.

(M8) Number of lesions surgically evaluated: measured through interrogation of clinic data.

(M9) Number of clinic visits attended: (routinely scheduled and fast-tracked unscheduled clinic visits) measured through clinic data.

(M10) Resource use: Costs to the health system and to patients in each arm of the trial will be estimated using an online resource use diary. The diary will be used to document and measure health service use - such as doctors’ clinic visits, other health practitioner consultations, imaging and other tests, hospital visits, and time taken to take and submit images for teledermatology. The diary will also document days out-of-role (including paid and unpaid work) and travel costs. The diary will be based on existing resource use questionnaires and the patient diary used in the MEL-SELF pilot study.

(M11) Carbon emissions: carbon costs of resources used, estimated using established carbon accounting methods [35, 36].

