### Assignment of interventions: allocation

#### Sequence generation {16a}

Participants will be randomly assigned to either control or intervention arms with a 1:1 allocation ratio. Minimisation will be used to ensure the study groups are balanced on key prognostic factors:
Specialist versus GP led clinic (two specialist clinic sites = Melanoma Institute Australia/Royal Prince Alfred Hospital and one GP led site Newcastle Skin Check)Patient age (age groups = 18–39, 40–70, 71+)Gender (male, female, other)Melanoma stage (Stage 0, IA, IB, IIA, IIB, IIC)Risk of a subsequent new primary melanoma (1-year absolute risk score < 5%, 5–10%, > 10% [48]).Dysplastic naevus syndrome (yes or no).

Within the intervention arm, participants will be randomised 1:1 to one of the two models of mobile dermatoscope (see Fig. 4). The method of randomisation to type of device will be by permuted blocks of varying size and stratified by key variables that might influence adherence with the device (potential confounders for the secondary outcome being evaluated for this comparison): site, age, and gender. The ratio will be adapted depending on adherence with submission of images that are of sufficient quality for teledermatology reporting. After 60 participants have been randomised into the intervention group, we will measure the proportion of intervention participants who have had an image reported on at one month after their baseline images (post randomisation) were due. If there is > 30% absolute difference in the proportion of intervention participants who have had an image reported on, participants who are subsequently enrolled will be randomised 2:1 to the dermatoscope model where more participants had an image reported on. If there is > 50% absolute difference in the proportion of intervention participants who have had an image reported on, then all participants who are subsequently enrolled will be randomised to dermatoscope model where more participants had an image that was reported on.

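### The planned routine-visit interval, checked at eligibility, is not a named covariate for the number of clinic visits (M9), which costs that comparison precision but does not bias it

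*Protocol article*

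**What the plan says.** **Outcome.** The protocol article (Outcomes {12}, Secondary outcomes) lists "M9) Number of clinic visits attended: (routinely scheduled and fast-tracked unscheduled clinic visits) measured through clinic data".

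**Model.** Under Statistical methods {20a}, Secondary outcomes, "In general, Poisson regression will be used for count variables". No covariates are attached to that statement. The open-ended wording about further prognostic covariates in the same section belongs to the linear models for continuous outcomes.

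**Interval.** Eligibility criteria {10} admit only patients whose routine visits at the treatment centre are no more often than every six months, with at least one such visit booked in the coming year. Intervention description {11a} expects control-arm visits to be "likely to be at intervals between 6 and 12 months". So the interval has to be looked at before randomisation, and it varies between participants.

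**Where it is absent.** Sequence generation {16a} states "Minimisation will be used to ensure the study groups are balanced on key prognostic factors" and lists clinic type, age group, gender, stage, new-primary risk and dysplastic naevus syndrome. For the primary outcome's adjusted model, "These will include age, sex, specialist/GP clinic, melanoma substage, subsequent new primary melanoma risk score [48] and dysplastic nevus syndrome". For time to diagnosis, "we will include the same covariates as for the primary outcome". The visit interval is in none of these lists.

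**The concern.** M9 adds scheduled and unscheduled visits. Both arms keep their usual scheduled visits (Intervention description {11a}), so any difference between arms should come mainly from the unscheduled part. The scheduled part is largely fixed by a clinical plan made before randomisation. In an unadjusted comparison it is mostly noise, and a baseline covariate could remove much of it.

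The covariates that are named were chosen as risk factors for melanoma. They predict who develops a lesion, not how often someone is booked to attend. At stake is the precision of the visit comparison, which is a stated secondary objective (Resource use) and bears on the trial's hypothesis about healthcare consumption.

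**Working it through.** The plan gives no figure for M9 to reproduce: no visit rates, interval mix or attendance. Everything below except the number of participants is an assumption.

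**Inputs**
- Participants: 225 per arm, from Sample size {14} (300 per arm less 25% dropout).
- Share on 6-monthly visits: q = 0.5, the rest yearly (assumed).
- Attendance at each scheduled visit: a = 0.9 (assumed).
- Unscheduled visits per person-year: u = 0.2 in control; 0.5 or 0.35 in intervention (assumed), Poisson distributed.

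**Step 1. Mean visits.** Mean = a(1 + q) + u.
- Control: 0.9 × 1.5 + 0.2 = 1.55.
- Intervention: 1.35 + 0.5 = 1.85, or 1.35 + 0.35 = 1.70.

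**Step 2. Variance of one person's count.**
- Between intervals: q(1 − q)a² = 0.25 × 0.81 = 0.2025.
- Attendance within interval: (1 + q)a(1 − a) = 1.5 × 0.09 = 0.135.
- Unscheduled: u.
- Control: 0.2025 + 0.135 + 0.2 = 0.5375, and variance/mean = 0.5375/1.55 = 0.35.
- Intervention at 0.5: 0.8375, and variance/mean = 0.8375/1.85 = 0.45.

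A Poisson model assumes a ratio of 1, so these counts are clearly under-dispersed.

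**Step 3. Standard error of the log rate ratio, 0.2 versus 0.5.** SE² = V₀/(n·m₀²) + V₁/(n·m₁²).
- Robust, unadjusted: 0.5375/(225 × 1.55²) + 0.8375/(225 × 1.85²) = 0.000994 + 0.001088, so SE = 0.0456.
- Robust, adjusted (drop 0.2025 from each variance): 0.335/540.56 + 0.635/770.06 = 0.000620 + 0.000825, so SE = 0.0380 (0.0381 in simulation).
- Reduction: 1 − 0.0380/0.0456 = 17%.
- Plain Poisson: 1/(225 × 1.55) + 1/(225 × 1.85) = 0.002867 + 0.002402, so SE = 0.073 with or without the interval in the model.

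**Step 4. Power, two-sided 5%, robust standard errors.** Power = Φ(log rate ratio/SE − 1.96).

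| Unscheduled visits | Log rate ratio | SE unadjusted → adjusted | Power unadjusted → adjusted |
|---|---|---|---|
| 0.2 v 0.5 | ln(1.85/1.55) = 0.177 | 0.0456 → 0.0380 | 97% → 99.6% |
| 0.2 v 0.35 | ln(1.70/1.55) = 0.092 | 0.0453 → 0.0370 | 53% → 71% |

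Simulation agrees: about 97% to 99.5% in the first row, and about 53–57% to 71–74% in the second.

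**Step 5. Plain Poisson standard errors.** The reported interval does not narrow. For 0.2 versus 0.5, simulated power goes from 76% to 83%, because the estimate itself varies less. For 0.2 versus 0.35 at 300 per arm it falls from 16–26% to 12–17%, depending on the interval mix. In that setting robust errors give 64–69% unadjusted and 81–84% adjusted.

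**Step 6. Sensitivity.** With 30–70% on 6-monthly visits, attendance 85–95% and 0.1–0.6 unscheduled visits, the interval explains 16–57% of the variance in total visits. The adjusted standard error is 0.66–0.92 of the unadjusted one.

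**The case against.** **The analysis plan may supply it.** The article defers full methods to a separate statistical analysis plan, and covariates for a count model are a natural item there. This stands: the Poisson sentence is a general statement, and nothing in the protocol contradicts itself. What remains is a recommendation. The covariate sets the article does name omit the interval, so carrying them over to M9 would not supply it, and the interval has to be captured before randomisation to be usable.

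**Stage and clinic type are proxies.** Partly true. The Background says recommended intervals depend on stage, and both stage and clinic type are already listed. But the interval is left to each clinician, so they capture only some of it. The working gives the interval its full effect without those covariates, so the extra gain over a model containing them would be smaller.

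**One model term does not deliver the gain.** Correct for plain Poisson standard errors, as Step 5 shows. The covariate has to be paired with a variance estimate that respects the under-dispersion.

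**Stronger readings.** A reader might infer more from the omission in four ways.
- *Chance imbalance would pass for an intervention effect.* At 300 per arm the between-arm difference in the 6-monthly share has SD √(2 × 0.25/300) = 0.041. A 2-SD imbalance moves mean visits by 0.082 × 0.9 = 0.07. The unadjusted standard error of the mean difference is √((0.5375 + 0.8375)/300) = 0.068, so the confidence interval already allows for it.
- *Time to diagnosis (M2) is compromised.* The sample-size rates put (6 − 1)/6 = 83% to (8 − 1)/8 = 88% of control-arm melanomas at scheduled visits. But M2 also covers keratinocyte cancers, and adding the interval moved simulated M2 power by only 0 to 2 points.
- *The primary outcome (M1) is affected.* The interval explains only about 0.1–1.2% of its variance (assumed rate ratios 1.5 to 3).
- *The cost analysis (M10) is deficient.* Its methods are deferred to a separate health economic plan.

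**Conclusion.** The point holds for M9 only. A baseline value that eligibility screening must already examine, and that separates about one from two scheduled visits in follow-up, is in no named covariate set and is not a minimisation factor. There is no bias, no error in the stated sample size and no effect of note on the primary outcome.

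The loss is precision on a secondary outcome: about 17% of the robust standard error in the central scenario, and 8–34% across the range in Step 6. It matters little if the unscheduled-visit contrast is large (power is already about 97%) and noticeably if it is small (about 53% against 71–73%). All of this rests on an assumed interval mix, attendance and unscheduled rates, and on robust or dispersion-corrected standard errors. That the interval strongly predicts total visits is a likely inference, not something the documents show.

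**What to change.** Record each participant's planned routine-visit interval (6-monthly or longer) before randomisation. Prespecify it as a covariate in the M9 count model, and state that M9 uses robust or dispersion-corrected standard errors because visit counts will be under-dispersed relative to Poisson. The statistical analysis plan is a suitable place for the model statement.

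The cost is one recorded item, already looked at for eligibility, and one model term. Adding the interval to the minimisation factors is optional, since a seventh factor for a secondary outcome is a matter of design preference. The M1, M2 and M10 models need no change on this ground.

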#### Costing analysis

Using a societal perspective, we will identify, measure and value all resources used to estimate the costs to patients, informal caregivers, to the health system, and to the environment (carbon emissions using relevant methods) for the intervention and control groups [35]. All costs associated with SSE, skin surveillance and management of newly identified lesions, out of pocket costs, opportunity costs and carbon costs will be included [11]. A detailed data health economics analysis plan will be developed and published separately.

